### Randomisation and treatment allocation

Based on the "ranuni" random number generator of the SAS/STAT^® ^software, subjects will be randomly allocated to the interventions under study by block-randomisation stratified by centre (investigator). Both the centres and subjects will be coded by simple numbers unidentifiable by subjects, investigators and external persons. The random list will be sent to the Charite' central pharmacy which will prepare sealed, sequentially numbered boxes containing the study medication and send them to the centre. When a subject agrees to participate, the investigator opens the lowest numbered box and gives him/her the study medication. Each centre will keep a log file with all randomised subjects. If a subject withdraws his/her consent or discontinues to the study, he/she may not be included again. The planned flow of participants through the homeopathic drug proving trial is illustrated as flowchart in Figure 2.

**Figure 2 F2:**
[figure not shown]
**Flow of participants through the homeopathic drug proving trial**.

### Intervention

Subjects in the intervention group are instructed to take five globules of the trial drug (potency C12), five times per day for a maximum of five days (5×5×5). The study medication is obtained from DHU (Germany), produced according to the Hahnemannian method [17]. Subjects are asked to stop taking the medication, in agreement with their investigator, if they experience any of a predefined set of proving symptoms (for definition see Table 1). Placebo consists of pure sucrose globules (DHU, Germany) that are not potentiated nor impregnated with alcohol. The administration scheme is identical in the placebo control group to that of the intervention group.

**Table 1 T1:** Criteria for proving symptoms and characteristic symptoms

Criteria for proving symptoms	Criteria for characteristic symptoms
New symptoms: the symptom is unfamiliar and has not been observed within the last year or during the run-in-period	Characteristic symptoms are defined as proving symptoms with a strongly individualistic character:

Study participant or study physician classify the symptom as new or unusual	Symptoms affecting the whole organism of one or more study participant

The study physician classifies the symptom as new in his final evaluation	Symptoms affecting different organs or organ systems of one or more study participant

A strong aggravation or modification of present (familiar) symptoms	Symptoms accompanying a variety of other symptoms

Present familiar symptoms that have disappeared during the proving (cure)	Symptoms that occur during the trial, which appear strange, peculiar or unique to one or more study participants

	Familiar symptoms from the past or present that have been cured or strongly alleviated

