**Method:**

Multi-centre, randomised, double-blind, placebo-controlled phase 1 trial with 30 healthy volunteers. The study consists of a seven day run-in period, a five day intervention period and a 16 day post-intervention observation period. Subjects, investigators and the statisticians are blinded from the allocation to the study arm and from the identity of the homeopathic drug. The intervention is a highly diluted homeopathic drug (potency C12 = 10^24^), Dose: 5 globules taken 5 times per day over a maximum period of 5 days. The placebo consists of an optically identical carrier substance (sucrose globules). Subjects document the symptoms they experience in a semi-structured online diary. The primary outcome parameter is the number of specific symptoms that characterise the intervention compared to the placebo after a period of three weeks. Secondary outcome parameters are qualitative differences in profiles of characteristic and proving symptoms and the total number of all proving symptoms. The number of symptoms will be quantitatively analysed on an intention-to-treat basis using ANCOVA with the subject's expectation and baseline values as covariates. Content analysis according to Mayring is adapted to suit the homeopathic qualitative analysis procedure.

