## Methods

### Study design

The homeopathic drug proving trial is to be conducted as a multi-centre, randomised, double-blind, placebo-controlled phase 1 trial. Subjects and investigators are not only blinded to the group allocation process but also to the identity of the drug.

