#### Questions to investigators

A "How would you estimate your subject's sensitivity to homeopathic remedies in general?" - Response options: same as above; B: "What is your expectation about your subjects reaction to the homeopathic drug?" - response options same as above.

After starting the trial, subjects are required to document daily any new or uncommon symptoms in a semi-structured trial diary accessed through a secure internet connection. It will provide a head-to-feet structure to be filled in with free text. Every third day each subject will be contacted by phone by his or her investigator. This optimises the homeopathic quality of documentation, which is considered crucial for a successful HDT [16]. A very detailed description of symptoms experienced by the subjects is essential for the quality of the homeopathic drug proving trial. Of special importance are precise descriptions of locations, sensations, modalities, concomitant symptoms, changes in mental or emotional state. Any strange, individual, uncommon and peculiar symptoms observed should be documented as these are considered most important for the homeopathic purpose. Investigators are only permitted to read and separately comment on the documentation of their subjects. The purpose of the supervision by the investigators and the additional documentation is to highlight special symptoms, improve documentation or mark special observations as is common in HDP. Investigators are not able to change the documentation of their subjects. Their documentation is saved and stored separately.

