## Classification as phase 1 trial

According to the German drug regulations, a homeopathic drug proving trial is a phase 1 trial. The objective of a conventional phase 1 trial is to assess the safety and to gain knowledge about their pharmacological dynamics in a small number of subjects. In contrast, the aim of a homeopathic drug proving trial is to identify new symptom patterns to identify therapeutic indications according to the law of similars and enhance the homeopathic knowledge and *materia medica *[20]. The subjects are usually doctors or students trained in homeopathy and not simply healthy volunteers.

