## Informed consent and blinding

Another aspect is that in conventional trials it is necessary to inform subjects and investigators about the identity of the drug, the risks and potential benefits. In an HDP this has to be hidden from the subjects and investigators to avoid bias in detecting and reporting symptoms. After lengthy discussions regarding our study, the Berlin ethics commission and the German health authorities agreed on keeping the study blinded for the subjects and investigators, but insisted on reporting the identity of the trialled substance, its risks and potential benefits to the authorities. This makes the whole procedure more complicated, because most materials (e.g. study protocol, investigators brochure) have to be produced in a blinded and a non-blinded version. We decided that only two members of the study team (the principal investigator and one study nurse) would know the identity of the drug to minimize the risk of involuntarily disclosing the drug on trial.

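### The placebo globules are specified as unimpregnated and matched to the drug only by appearance, so the arms appear to differ in vehicle as well as in the C12 drug

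*Protocol article*

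**What the plan says.** The study design section describes a "multi-centre, randomised, double-blind, placebo-controlled phase 1 trial". The Intervention section then sets out the two products:

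- **Drug:** "The study medication is obtained from DHU (Germany), produced according to the Hahnemannian method". It is taken as "five globules of the trial drug (potency C12), five times per day for a maximum of five days".
- **Placebo:** "Placebo consists of pure sucrose globules (DHU, Germany) that are not potentiated nor impregnated with alcohol". It follows the same administration scheme.

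The abstract (Method) makes the only statement about matching: "The placebo consists of an optically identical carrier substance (sucrose globules"). The article does not mention smell or taste.

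On the source of the data, the Procedures text says that "subjects are required to document daily any new or uncommon symptoms in a semi-structured trial diary". The primary outcome (Outcome parameters) is the number of characteristic proving symptoms per subject. Investigators who are still blinded code it from those diaries (Qualitative analysis). The Discussion says of such trials: "The subjects are usually doctors or students trained in homeopathy and not simply healthy volunteers". It also explains that the drug's identity is withheld "to avoid bias in detecting and reporting symptoms".

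**The concern.** A placebo should differ from the drug only in the component under test. Here the specification itself appears to add a second difference, the impregnating vehicle. Two consequences follow.

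1. **Attribution.** The null hypothesis in the Background concerns symptoms provoked by the drug at potency C12. If one arm receives impregnated globules and the other does not, the comparison tests drug plus vehicle against neither. This holds whether or not anyone notices the difference.
2. **Blinding.** If the vehicle leaves a taste or smell, subjects could form a belief about their arm once dosing starts. The outcome begins as free text that they write themselves. The article presumes that expectation could be related to the outcome, and it measures expectation only at baseline.

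With 24 to 30 subjects and a single primary comparison, a modest reporting shift in one arm could raise the chance of a false positive finding. No analysis can repair a mismatched control afterwards.

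**Working it through.** **Step 1. The two products side by side (Intervention; abstract, Method).**

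| Feature | Drug | Placebo | Stated or inferred |
|---|---|---|---|
| Potentised | yes, C12 | no | stated |
| Impregnated with alcohol | presumably yes | no | placebo stated; drug inferred |
| Appearance | same | same | stated |
| Taste and smell | not given | not given | not stated |

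Denying impregnation for the placebo makes sense mainly if the drug globules have it. That is the natural reading, but it remains an inference.

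**Step 2. Exposure (Intervention).** 5 intakes per day × 5 days = up to 25 intakes. At 5 globules each, that is up to 125 globules.

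**Step 3. Does the plan contain something that corrects a belief formed during dosing?**

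- Coding is blinded, with second review and two independent coders (Qualitative analysis). This protects the coding step. It does not change what the subject wrote.
- The ANCOVA adjusts for the subject's expectation and the baseline value (Quantitative analysis). Both precede dosing, so neither captures a later guess.

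**Step 4. The plan's own sample size figure.** The inputs are 20 vs 15, SD 4, two-sided 5%, 24 analysable of 30 (Sample size calculation), with 1:1 allocation assumed. The noncentrality is difference / (SD × √(2/n)).

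- n = 11 per arm: power 79.6%.
- n = 12 per arm: 5 / (4 × √(2/12)) = 3.06, power 83.3%.
- 24 / (1 − 0.20) = 30.

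The stated sample size reproduces and is not in dispute. It supplies the SD and n used below.

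**Step 5. Illustration of bias from unblinding.** Assume no true effect and SD 4. A share f of the drug arm detects the product, and each of these subjects contributes b extra characteristic symptoms. The mean shift is f × b. Neither f nor b is in the documents.

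If the shift applied uniformly to the whole drug arm, the noncentral t gives:

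| Mean shift | 12 per arm | 15 per arm |
|---|---|---|
| 1 | 9.0% | 10.1% |
| 2 | 21.6% | 26.2% |

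If only the detecting subjects shift, the drug arm's variance rises by b² × f × (1 − f). For f = 0.4 and b = 5 this is 25 × 0.24 = 6, so its SD becomes √(16 + 6) = 4.69 and the rejection rate falls somewhat. Simulated two-sided 5% t-tests give:

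| f | b | Mean shift | 12 per arm | 15 per arm |
|---|---|---|---|---|
| 25% | 2 | 0.5 | about 6% | about 6% |
| 20% | 5 | 1.0 | 8.3% | 9.4% |
| 25% | 5 | 1.25 | about 10% | about 12% |
| 40% | 5 | 2.0 | about 19% | about 23% |

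The range runs from barely above the nominal 5% to more than four times it, depending wholly on the assumptions.

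**The case against.** **What stands against the point.**

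- Nothing states that the drug globules carry alcohol when taken, and nothing says that any residue can be tasted or smelled. A reader might infer that subjects will recognise the drug. The article supports only that they might, if a residue remains.
- Each subject receives one product, so there is no side-by-side comparison within a person. Recent homeopathic treatment (the previous six weeks) is an exclusion criterion.
- A reader might infer that the subjects are trained provers. Eligibility requires only medical doctors or medical students. Training in homeopathy comes from a general remark qualified by *usually*, and earlier participation in a proving is simply recorded at baseline.
- A reader might take the primary outcome to be raw self-report. It is a count coded by blinded investigators, and extra diary entries must meet the Table 1 criteria to count.
- The article says only that the authors presume expectation could be related to the outcome, not that it is known to drive symptom counts.
- The upper illustration gives each detecting subject 5 extra characteristic symptoms, which equals the trial's entire target difference (20 − 15). It also uses a t-test, whereas the planned model is an adjusted ANCOVA.
- Product specifications and a check of blinding may sit in the full protocol. Their absence from an article is not an error.
- No passage suggests that the solvent on five globules would itself cause symptoms.

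**What remains.** The placebo's composition is stated, not omitted. Fuller documents could add matching data, but a placebo specified as unimpregnated stays unimpregnated. The objections limit how likely and how large the bias is. They do not make the vehicle the same in both arms, and they do not let blinded coding or baseline adjustment correct the diary text.

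**Conclusion.** The point holds in limited form. As specified, the placebo is unimpregnated and is claimed to match the drug only by sight. On the natural reading, the arms differ in vehicle as well as in the potentised drug, so a positive result could not be assigned cleanly to the C12 preparation. Loss of blinding is a possibility that depends on an undocumented taste or smell. Its effect on the false-positive rate could lie anywhere from about 6% to about 23% under the 25%-and-2 and 40%-and-5 scenarios, and those inputs are assumptions.

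It would go too far to conclude that blinding fails or that the primary result is invalid, because the documents show neither. This is a cheap improvement, worth making before the medication is packed, and not an essential correction.

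**What to change.** In the Intervention section, specify the placebo as sucrose globules from the same manufacturer, impregnated with the same unpotentised solvent without the drug. State that both products match in appearance, smell and taste, and bring the abstract into line.

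As a minor addition, ask each subject and investigator before unblinding which arm they believe was given, and report the answers by arm.

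The cost is a changed order for about 15 placebo boxes (half of 30, assuming 1:1 allocation), updated product documents and one extra question. If placebo has already been packed, it would have to be re-supplied. The sample size and the analysis model need no change.

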### Outcome parameters

The primary outcome parameter is the number of characteristic proving symptoms per subject, derived from the qualitative data analysis of the homeopathic proving drug compared to placebo within three weeks after the initial dose of the drug or the placebo is administered. Definitions of characteristic symptoms are given in Table 1.

Secondary outcome parameters are: the total number of proving symptoms irrespective of whether they are characteristic or not (definition of proving symptoms see Table 1) and the number of serious adverse events.

Qualitative differences in the profiles of characteristic proving symptoms from the homeopathic drug and the placebo will also be compared and the inter-coder reliability of the qualitative evaluation of characteristic proving symptoms will be calculated.

### Sample size calculation

It is planned to include 30 healthy volunteers. Assuming a drop out rate of 20%, 24 subjects will be available for analysis. In this study, an unpaired t-test with a two-sided level of 5% has a power of 80% to detect a group difference of 20 ± 4 vs 15 ± 4 (mean ± standard deviation) characteristic proving symptoms.

### Analysis

The trial diaries with the data entries of subjects and investigators provide the data for the qualitative and quantitative analysis. The qualitative analysis will be carried by experienced homeopathic doctors trained in qualitative research methodology, the quantitative analysis by a statistician.

## Qualitative analysis

Data are coded by content analysis according to Mayring [18] and analysed using Atlas.ti 5.2 software. Homeopathic definitions for proving symptoms and characteristic symptoms (Tables 1 and 2) serve as predefined categories for the coding processes.

**Table 2 T2:** Coding guideline for the homeopathic drug proving

Categories +Subcategories	Definition	Example	Code (Example)
**Locality**	Anatomic location where the symptom appears.	Nose, chest.	**QL**
+ specification			+ QL-nose
			+ QL-chest
**Sensation**	Sensation that is observed in a symptom.	Stitch, dryness.	**QS**
+ specification			+QS-stitch
			+QS-dryness
**Modality**	Factors which aggravate (agg) or ameliorating (amel) a symptom	Aggravation by cold wind, amelioration with warmth.	**QM**
+ specification			+QM-agg-cold-wind
			+QM-amel-warmth
**Concomitant**	Symptoms that typically accompany other symptoms.	Headaches accompany anticipatory anxieties.	**QC**
+ specification			+QC-headaches
**Times**	Times when symptoms appear or disappear	Headaches at 7 am.	**QT**
+ specification			+QT-7am
**Mind**	Mental or emotional disturbances.	Fear, sadness	**QM**
+ specification			+QM-fear
			+QM-sadness
**Clinical finding**	Clinical findings and signs.	Eczema, sweating	**QF**
+ specification			+QM-eczema
			+QM-sweating

Q = Quality; L = Locality; S = Sensation; M = Modality; C = Concomitant; T = Times; M = Mind; F = Clinical findings; agg = Aggravation; amel = Amelioration

The qualitative data analysis consists of three steps: categorisation of proving symptoms, categorisation of characteristic symptoms, and context analysis (Figure 3).

**Figure 3 F3:**
[figure not shown]
**Data analysis process in homeopathic drug proving trial**.

After closing the trial, the investigators obtain the complete body of text from the trial diary for each of their subjects and are asked to categorise "proving symptoms" in accordance to the prescribed definitions. Subsequently, a second investigator reviews coding and categorisation. In cases of contradictory categorisations, a review committee of two investigators will decide on the categorisation. At the end of this process, a list of proving symptoms for each subject will be compiled.

The categorisation of characteristic symptoms is the next step. To identify characteristic symptoms which occurred in more than one subject, an inter-subject comparison of each study arm is needed. However, investigators will still be blinded from the treatment allocation. This analysis is performed independently by two experienced investigators. The inter-coder reliability is calculated by the study statistician. The data is further structured into the following categories: localities, sensations, modalities and concomitants, times, mind and clinical findings.

Profiles of characteristic symptoms are compiled for both groups which can now be compared qualitatively.

Context analysis is the final part and will be conducted when the drug identity has been revealed at the end of the trial. The results will be related to the traditional and scientific knowledge available on the drug being investigated and discussed in the research team. The aim is to find out whether the data fits into the body of knowledge already available on the particular drug and its plausibility.

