## Quantitative analysis

The main outcome will be analysed on an intention-to-treat basis by univariate analyses of covariance (ANCOVA) which includes the group (two levels), subject's expectations (ordinal with 4 levels) and the respective baseline value (linear) as covariates. From these model we will estimate the baseline adjusted treatment effect and its 95% confidence interval (CI). The reported *P*-value will be based on a two-sided t-test within this model, and a *P *< 0.05 will be considered significant. Missing values will be multiply imputed according to Rubin's suggestions [19]. In detail, 20 multiple copies of the original data set will be generated, replacing missing values by a randomly generated value according to the MCMC algorithm. Each copy will be analysed as a complete data set with the abovementioned ANCOVA model and the results will be combined appropriately. Sensitivity analyses will include some extensions of the statistical model, in this way modelling the centre as a random factor and adding the center's expectation (ordinal with 4 levels) as an additional fixed factor.

Analyses of the secondary outcome parameters will rely on the same statistical models, hereby replacing the baseline value of the main outcome parameters by the baseline value of the parameter under consideration.

All analyses will be performed using SAS/STAT^®^.

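### Characteristic symptoms are matched between subjects within each arm before the primary counts exist; to the extent this matching feeds the counts, the ANCOVA test exceeds its 5% level

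*Protocol article*

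**What the plan says.** Under Outcome parameters, "The primary outcome parameter is the number of characteristic proving symptoms per subject", and the count is taken from the qualitative data analysis. That analysis has three steps: categorising proving symptoms, categorising characteristic symptoms, and context analysis. Within the second step, for symptoms found in more than one subject, "an inter-subject comparison of each study arm is needed. However, investigators will still be blinded from the treatment allocation". Two experienced investigators do this independently, and the statistician calculates their agreement. The profiles of the two groups are described afterwards, as a further product.

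Table 1 (under Intervention) lists five criteria for a characteristic symptom. Three of them refer to one or more participants, for example "Symptoms affecting different organs or organ systems of one or more study participant". None requires that a symptom recur.

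Under Quantitative analysis, "The main outcome will be analysed on an intention-to-treat basis by univariate analyses of covariance (ANCOVA)", with group, the subject's expectation and the baseline value in the model. The sensitivity models add centre as a random factor and the centre's expectation.

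**The concern.** Nobody can compare subjects within each arm without having the diaries sorted by arm. The statement that investigators remain blinded can then only mean that the arm labels are hidden; who belongs with whom is disclosed. The article does not say how the two statements fit together.

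If a symptom counts for a subject because another member of the same arm reported it, that subject's count depends on who else is in the arm and on how large the arm is. The ANCOVA has no term for this, and could not have one, because an arm-level coding effect cannot be separated from the group effect. Both covariates are measured before treatment and cannot absorb it. Inter-coder agreement does not detect it either, since both coders make the same arm-wise comparison and can agree on the same artefact. At stake is whether a significant P-value for the primary outcome could arise partly from the scoring step.

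**Working it through.** **1. The plan's own figure.** Inputs from Sample size calculation: "It is planned to include 30 healthy volunteers", 20% drop-out, 24 analysed, two-sided 5%, and "20 ± 4 vs 15 ± 4 (mean ± standard deviation) characteristic proving symptoms". The standardised difference is (20 − 15)/4 = 1.25. With 1:1 allocation assumed, the exact unpaired t-test has power 79.6% at 11 per arm and 83.3% at 12 per arm. So 12 per arm is the smallest size reaching 80%, and 24/0.8 = 30. The figure reproduces. It assumes independent subjects.

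**2. How matching links the counts.** The document gives no symptom frequencies, so these are assumptions: 25 proving symptoms per subject, 300 equally likely symptom types, and a symptom scores only if at least one other member of the arm of size n has it. The chance that a given symptom scores is about 1 − (1 − 25/300)^(n−1).
- n = 15: 1 − (11/12)^14 = 0.704, or 25 × 0.704 = 17.6 scored symptoms.
- n = 18: 1 − (11/12)^17 = 0.772, or 19.3.
- n = 12: 1 − (11/12)^11 = 0.616, or 15.4.

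With equal arms the expected counts are equal, but matches are shared by the members of an arm. The arm means therefore vary more than the within-arm SD implies. At 18:12 there is in addition a null difference of 19.3 − 15.4 = 3.9 symptoms, against a planned effect of 5. This is the extreme case in which every symptom needs a match.

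**3. Simulated type I error.** Setting: no drug effect, between-subject CV 30%, uniform or Zipf (0.8) symptom frequencies, 1,500 trials per setting, two-sided t-test. A stated share of symptoms needs a match and the rest score on their own.

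| Share needing a match within the arm | 12:12 and 15:15 |
|---|---|
| all | 13-20% |
| half | 10-11% |
| a fifth | 6-7% |
| none | 5% |

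Matching over all subjects pooled gives 5-6%. At 18:12, if all symptoms need a match, the rate is 27-46%. The Monte Carlo standard error is √(0.05 × 0.95/1500) = 0.6 percentage points near 5%, and larger at higher rates. Repeat runs moved individual figures by up to about two points without changing the pattern.

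**4. How likely unequal arms are.** The Randomisation section gives blocks stratified by centre, and each centre has at most three subjects. The ratio is not stated. Assume ten full centres of three, each splitting 2:1 in a random direction. One arm's size is then 10 + Binomial(10, ½). The probability of 18:12 or worse is 2 × (45 + 10 + 1)/1024 = 11%. The probability of 20:10 is 2/1024 = 0.2%.

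**5. A judgemental route.** Suppose coders working on two known groups apply slightly different thresholds, so that each arm's counts shift by a common amount with SD τ. With SE = 4√(2/n), the rejection rate is 2·P(T > t_crit·SE/√(SE² + 2τ²)) on 2n − 2 degrees of freedom. For n = 12 and τ = 1: SE = 1.633, the ratio is 1.633/√(2.667 + 2) = 0.756, the effective cut-off is 2.074 × 0.756 = 1.568, and the rate is 13.1%. With τ = 2 it is 31.1%. For n = 15 the rates are 15.2% and 35.5%. Nothing in the document supports any value of τ, so these figures are illustrations only.

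**The case against.** The strongest reply is that Table 1 does not make recurrence a criterion. A symptom that qualifies in one subject gains nothing from a match in another. If coders follow Table 1 strictly, the comparison changes no one's count and the 5% level holds. This stands as a limit on the size: the all-matching figures are an upper case for the matching route, not an estimate.

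A second reply is that the sentence may mean finding which characteristic symptoms recur, as input to the group profiles, which Outcome parameters lists apart from the count. This cannot be excluded, and Figure 3, which shows the process, is not available here. It is the weaker reading, because the text puts the comparison inside the categorisation step, before the profiles are compiled, and describes no other step that yields the primary count.

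Third, the Discussion (Qualitative analysis) admits that a failed qualitative analysis could bias the P-values, and plans independent double coding. The risk is acknowledged, but double coding does not remove an effect that both coders share.

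A reader might also infer that the coders are unblinded and will favour the drug. The document does not support that. Only the grouping is revealed; the arm labels and the identity of the drug stay hidden. Nor does it support error rates for very unequal arms as typical, since 20:10 is remote under 1:1 blocks.

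**Conclusion.** The concern holds in conditional form. As written, arm-wise comparison takes place before the primary counts are fixed, and any part of the count that rests on it breaks the independence the ANCOVA needs. Under the assumed symptom frequencies and equal arms, the inflation runs from none, if no symptom depends on matching, through one to two points if a fifth do and about a doubling if half do, to 13-20% if all do. The true share cannot be read from the document. The planned covariates, the sensitivity models and the agreement statistic do not correct it. An arm-level coder shift is a further possible route of unknown size. That the 5% level fails outright is not established. The point should be fixed; confidence is medium because of the alternative reading.

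**What to change.** Amend the Qualitative analysis section as follows.
1. For the primary count, code characteristic symptoms from single-subject lists, in random order, with no arm grouping shown.
2. Make any comparison for symptoms occurring in more than one subject across all subjects pooled, both arms together. Under no drug effect the counts are then exchangeable between arms, which restores the nominal level.
3. Lock the per-subject counts.
4. Only then group by arm, labels still hidden, to compile the secondary qualitative profiles.

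If the arm-wise comparison was always meant for the profiles alone, one sentence saying so, with the lock placed before it, is enough.

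The cost is wording and the order of work already planned; no extra staff and no change in sample size. The downside is that recurrence specific to one arm no longer contributes as such to the primary count and is reported only in the secondary profiles.
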